## Abstract

Uterine sarcomas can be difficult to differentiate from uterine fibroids due to many shared symptoms and imaging features, which can result in delayed or missed diagnosis, or over treatment. The ‘Development of a blood test for uterine Sarcoma – Diagnosis’ (DOORS-D) (ISRCTN14800787) and ‘Development of a blood test for uterine Sarcoma – Monitoring’ (DOORS-M) (ISRCTN14174468) studies aim to explore the role for circulating tumour DNA (ctDNA) to diagnose and to monitor uterine sarcomas. DOORS-D will recruit patients who have a suspected uterine sarcoma or large fibroid and are due to undergo surgery (hysterectomy or myomectomy) for a blood sample prior to surgery whereas DOORS-M will recruit patients who have been diagnosed with a uterine sarcoma in the previous 10 years for longitudinal blood sampling every 3–6 months over the course of the study. Information will be collated on patient characteristics and symptoms, tumour characteristics and diagnostic imaging, with representative images selected and analysed using large language models. Analysis of genomic/methylation profile of ctDNA samples collected from DOORS-M will be used to design a ctDNA-based ‘test’. Analysis of the samples collected from the participants recruited to the DOORS-D study will enable the accuracy of the ‘test’ to differentiate uterine sarcomas from fibroids to be determined. In addition, the opinions of patients with a suspected or confirmed sarcoma will be explored through semi-structured qualitative interviews. Purposeful recruitment strategy will ensure that the experiences of women from diverse socioeconomic, cultural and ethnic backgrounds are included. The results of the studies will be shared through conference presentations and peer-reviewed publications.

## Introduction

Uterine sarcomas are rare mesenchymal tumours that account for 3% of all uterine cancers and are often associated with a poor long-term prognosis [1]. Uterine sarcomas typically arise from myometrial smooth muscle or endometrial stroma, with leiomyosarcomas (LMS) being the most common subtype accounting for 60–70% of cases, followed by endometrial stromal sarcomas (ESS) at 10–20% [2]. Their myometrial, rather than endometrial, location makes diagnosis more challenging since biopsy of the endometrium is only able to detect 35% of LMS and 25% of ESS [3]. The other key diagnostic challenge is the difficulty differentiating a uterine sarcoma from uterine fibroids which are very common benign uterine growths affecting 40–80% of women [4], due to shared symptomatology [5]. Fibroids especially impact women aged 40–60 years, who have a 4–11 times greater risk than younger women (20–30 years) or older women (>60 years) [6]. Women of African ancestry also experience a higher incidence and prevalence of uterine fibroids compared to women from other races or ethnic groups, 30.6/1000 women-years compared to 8.9/1000 for White women [7].

Accurately differentiating between a uterine fibroid and a sarcoma is of paramount importance, not only to expediate oncology management of patients with a sarcoma, but to avoid procedures that could cause result in cancer dissemination and thereby worsening patients’ prognosis. Although the incidence of unexpected sarcoma at uterine fibroid surgery is low, 0.175 to 0.67% [5], it has been reported that 19% of unexpected sarcoma cases underwent a subtotal hysterectomy or open myomectomy [8]. Intraoperative pathology assessment can help with guiding patient management however, this is can be associated with diagnostic challenges [9], and appears to be less concordant with final histology compared to assessment of other gynaecological malignancies [10]. Laparoscopic myomectomy with morcellation in particular, is associated with a significantly lower 5-year recurrence-free survival rate compared to total hysterectomy for unexpected uterine sarcoma, 24.1% compared to 43.6%, with greater rates of peritoneal dissemination reported, 22.2% versus 0.0% [11]. Consequentially, the United States Food and Drug Administration (FDA) have advised morcellation within retrieval bags to prevent dissemination [12,13].

At present there is no specific blood test that can be used pre-operatively to differentiate between uterine sarcomas or fibroids. The tumour marker CA125 is not helpful [14]. LDH and its isoform LDH3 have been shown to be an independent predictor of LMS [15] although not validated for clinical use, and obesity can be a confounding factor increasing the false positive rate [16]. Other blood markers, such as C-reactive protein and absolute neutrophil count, have shown associations with sarcomas [17] however lack specificity. Imaging, in particular MRI, can be used to differentiate between uterine sarcomas and fibroids with a high level of diagnostic accuracy [18]. Features including peritoneal or lymph node metastases, high/intermediate on T2-weighted imaging, low apparent diffusion coefficient (ADC) and high intensity signal of diffusion weighted images were identified as having a strong association with uterine sarcomas [19]. Other features, such an irregular margin, haemorrhage and enhancement, were determined as being an indeterminate association [19], and it is reported that there is a greater challenge when differentiating degenerating or complex fibroids from uterine sarcomas [20]. PET-CT scans have been shown to have a greater ability to distinguish fibroids from sarcomas, sensitivity of 80.8% and specificity of 100% [21], however, such imaging would typically only be performed in cases where there was a high suspicion of sarcoma, therefore is unlikely to impact the unexpected sarcoma diagnosis rate.

The genomic profile of uterine sarcomas reveals a mixed picture with common somatic mutations, including *TP53* (56%) and *RB1* (51%) but also somatic copy number alterations (SCNAs), with whole genome duplication (WGD) identified in half of high-grade sarcomas [22]. Uterine fibroids are monoclonal tumours although 40–50% are reported to have detectable chromosomal abnormalities, and a recent genome wide meta-analysis has identified 46 novel genes associated with fibroids [23]. Genomic analysis, for example, shallow whole genome sequencing (sWGS) shows potential to discriminate between sarcomas and fibroids, with a pilot study reporting that the percentage of the genome affected by SCNAs in plasma of six patients with fibroids was lower than the proportion of the genome showing SCNA in patients with sarcoma [24].

Liquid biopsies based on circulating tumour DNA (ctDNA) are rapidly becoming established as a minimally invasive tool for diagnosis, guiding treatment regimens and monitoring for recurrence [25]. The evidence to support a role in the monitoring and detection of endometrial cancer recurrence is increasing [26–29] with a higher diagnostic accuracy compared to the currently available tumour markers, CA125 and HE4 [30]. The potential of the ‘liquid biopsy’ to monitor uterine sarcomas has been explored in previous studies where ctDNA has shown promise as a marker both in the monitoring [31–33] and diagnosis [24] of uterine sarcomas, although other analytes including microRNAs have also been shown to have potential as biomarkers [34]. Leiomyosarcomas were the most common histological subtype investigated and there was significant heterogeneity in terms of both laboratory approaches and the reporting of these approaches. Given the small number of uterine sarcoma cases in the majority of the studies to date, the proportion of cases with detectable ctDNA is currently unknown, and there is no cost-effective test that could give a result in a short time frame to guide patient management, thereby reducing pre-operative diagnostic uncertainty.

### Hypothesis

ctDNA is an acceptable test that can be used in routine clinical practice to diagnose and/or monitor uterine sarcomas.

## Materials and methods

### Ethical approval and trial registration

In order to address the two potential roles for ctDNA, two studies have been designed: Development of a blood test for uterine Sarcoma – Diagnosis (DOORS-D) and Development of a blood test for uterine Sarcoma – Monitoring (DOORS-M). Both studies have received ethical approval from the South Central – Berkshire B Research Ethics Committee (25/SC/0107 and 25/SC/0108) and have been registered on ISRCTN registry (https://www.isrctn.com/ISRCTN14800787 registered on 03/06/2025 and https://www.isrctn.com/ISRCTN14174468 registered on 04/06/2025). The study is being conducted by academics and clinicians with expertise in gynaecological oncology (EM), liquid biopsies and genomic analysis (JS/RA/CC/MW), pathology (ES), radiology (YG/ID) and health equity (ND). The study is sponsored by the University of Leicester (protocol numbers 1040 (DOORS-M), 1041 (DOORS-D) and opened for recruitment in July 2025. The clinical research teams will be notified of protocol modifications through the sponsor’s research governance team. The research team (EM/JS/CC/MW/ND) are employees of the study sponsor and have designed of the study and will conduct, analyse, and report the outcomes. Given the nature of the studies a Data Monitoring Committee will not be required, instead representatives from the sponsor’s research governance team will monitor the conduct of the study and ensure that all procedures and requirements are adhered to. Participant recruitment will continue until 31/01/2028 and data collection will be completed by 28/03/2028 (end of study), with additional follow-up data on patient outcomes collected up to 2 years following the end of the study. It is anticipated that the results of the qualitative aspects of the studies will be reported in 2026, whereas results from the clinical aspect of the studies will be reported in 2028.

### Public and patient involvement (PPI)

PPI groups and outreach events have been held with women from diverse ethnic backgrounds, including of Black ethnicity, to discuss the challenge of uterine fibroid management and the need to identify uterine sarcomas in a timely manner. The PPI group reported awareness of uterine fibroids but not sarcomas, and were supportive of the development of a blood test to guide diagnosis and management. The study design is similar to a previous cohort study developing a blood test to diagnose endometrial cancer recurrence, which was deemed a very acceptable test by the study participants [35]. A PPI group to advise the research team during the conduct of the study will be recruited.

### Study design

DOORS-D is a single centre case series study that is being conducted in an academic gynaecological oncology centre at the University Hospitals of Leicester. DOORS-D aims to investigate whether genomic alterations in plasma are able to distinguish between uterine sarcomas and uterine fibroids, with a secondary aim to investigate the potential of radiomics and large language models to diagnose sarcomas.

DOORS-M is a cohort study, collecting data and longitudinal samples from patients who have been diagnosed with a uterine sarcoma that aims to create genomic and methylation profiles for uterine sarcomas to identify signatures that could be used within a ctDNA ‘test’ to detect or predict recurrence. The lead recruitment site will be the University Hospitals of Leicester, Additional recruitment sites will be established however, no blood samples will be collected from the other sites, instead information on patient characteristics, archived tumour samples and sequencing results, and imaging will be collected.

Both studies include secondary objectives of exploring patients’ opinions and the psychological impact of ctDNA to diagnose/monitor uterine sarcomas. Table 1 includes the study objectives for the two studies.

**Table 1 pone.0339336.t001:** Objectives for DOORS-D and DOORS-M studies.

DOORS-D	
Primary objective	To investigate whether genomic alterations in plasma are able to distinguish between uterine sarcomas and fibroids
Secondary objectives	To investigate the ability of a ctDNA ‘test’ to detect uterine sarcomas To investigate the potential of Artificial Intelligence (AI) to diagnose uterine sarcomas To explore the psychological impact of ctDNA testing to guide uterine sarcoma diagnosis
**DOORS-M**	
Primary objective:	To create genomic and methylation profiles for uterine sarcomas
Secondary objectives:	To investigate the ability of a ctDNA ‘test’ to detect uterine sarcoma recurrence To investigate the potential of AI to diagnose uterine sarcomas To explore the psychological impact of ctDNA testing in uterine sarcomas follow-up To identify a symptom profile associated with uterine sarcomas

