**Fig 2 pone.0339336.g002:**
[figure not shown]
Participant timeline: Schedule of enrollment, interventions, and assessments for DOORS-M study.

Potential participants will be identified through their clinical care team, screened, and if eligible approached by a member of the research team for recruitment. Once recruited, information will be collected on a CRF to collate information on the patient’s demographics, previous medical history and sarcoma diagnosis/treatment. Tumour blocks from previous diagnostic or treatment biopsies will be requested for DNA extraction and WES, unless previously sequenced as part of the patient’s clinical care. A blinded pathological review will be undertaken by the study pathologist to confirm the diagnosis. Pre-operative imaging will undergo a blinded review following the same process outlined in DOORS-D, and representative images stored for future AI analysis. At recruitment the participant will have 20mls of blood collected for processing into plasma and storage for ctDNA analysis. Given the constant advances in the field we have not predetermined *a priori* the ctDNA analysis technique. Further blood samples will be collected at subsequent clinic appointments, or 3–6 monthly, for as long as the patient remains within the study. Only participants recruited at the University Hospitals of Leicester will undergo blood sampling due to logistic and financial constraints however, participants will consent to analysis of archival tumour tissue for DNA extraction, thereby expanding the number of sarcoma cases available for analysis. Recruitment from other sites will also involve CRF completion and participant interviews, thereby extending the geographical spread of the study. As with DOORS-D, a subset of participants will be recruited for a semi-structured qualitative interview to discuss their opinions and the potential psychological implications of using ctDNA to diagnose, and/or predict, sarcoma recurrence. The selection of participants will aim to capture a range of opinions and experiences and include an ethnically and socioeconomically diverse population.

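### DOORS-M plasma is used both to design the ctDNA test and to assess its detection of recurrence, with no stated separation, so any recurrence accuracy from a signature or cut-off chosen on that plasma would be optimistic

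*Protocol article*

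**What the plan says.** The protocol article gives DOORS-M three linked roles.

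- **Design of the test.** The Abstract says: "Analysis of genomic/methylation profile of ctDNA samples collected from DOORS-M will be used to design a ctDNA-based" test. DOORS-M plasma is therefore development material.
- **Search for a recurrence signature.** Under Study design, the DOORS-M profiles are meant "to identify signatures that could be used within a ctDNA ‘test’ to detect or predict recurrence".
- **Assessment of recurrence detection.** The first DOORS-M secondary objective in Table 1 is "To investigate the ability of a ctDNA ‘test’ to detect uterine sarcoma recurrence".

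The article also limits where other recurrence plasma could come from. On DOORS-D, the Abstract says: "Analysis of the samples collected from the participants recruited to the DOORS-D study will enable the accuracy of the" test to be determined, but only for telling sarcomas from fibroids. For the additional DOORS-M sites, Study design says that "no blood samples will be collected from the other sites". Study processes – DOORS-M repeats the point: "Only participants recruited at the University Hospitals of Leicester will undergo blood sampling". The DOORS-M target is 50 women (Sample size). The number who will give blood is not stated. The ctDNA technique is deliberately left open (Study processes – DOORS-M).

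**The concern.** For the diagnostic use, the Abstract puts design in one cohort and accuracy in another. For recurrence, both fall on the same cohort, and no second set of plasma is available in either study.

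If features or a cut-off are chosen because they separate women with and without recurrence, and are then scored on those same women, sensitivity and specificity are inflated. The inflation is greatest with few patients and many candidate features. Here there are at most 50 women with plasma, and the genomic and methylation candidates are not limited in advance.

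The hypothesis includes use of ctDNA to monitor uterine sarcoma in routine practice, and DOORS-M is the study that addresses that half. An inflated figure could make an uninformative signature look promising and affect whether, and with which test, the larger follow-on evaluation is run.

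**Working it through.** **The article's own figure.** The only precision figure is for DOORS-D: 20 sarcoma cases and sensitivity 0.95. The exact (Clopper-Pearson) interval for 19/20 has lower limit Beta⁻¹(0.025; 19, 2) = 0.7513 and upper limit Beta⁻¹(0.975; 20, 1) = 0.9987, a width of 0.2475. This agrees with the stated 0.751–0.999 and 0.247. It concerns diagnosis and says nothing about recurrence. No figure is given for recurrence.

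**Is there a second set of plasma for recurrence?**

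1. DOORS-D blood is taken once, before surgery, and is assigned to sarcoma versus fibroid.
2. DOORS-D women found to have a sarcoma or STUMP are offered DOORS-M (Study processes – DOORS-D). If they join, their later plasma becomes DOORS-M plasma.
3. Other DOORS-M sites give tissue, sequencing results, imaging and clinical data, but no blood.

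The Leicester DOORS-M plasma is therefore the only plasma in which recurrence detection can be assessed.

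**How large could the optimism be?** The article gives neither the recurrence split, nor the number with blood, nor the number of candidate features. All three are assumed below.

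*Best single feature.* There are 1,000 null replicates per setting, with independent noise features and one value per patient. For each feature, AUC = [R₁ − n₁(n₁+1)/2] / (n₁n₀), where R₁ is the rank sum in the n₁ women with recurrence. The feature with the largest AUC in either direction is kept, and the cut-off maximises sensitivity + specificity − 1 in the same women. The true AUC is 0.50.

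| Recurrence v none (assumed) | 5 features | 10 features | 40 features |
|---|---|---|---|
| 25 v 25 | 0.63 | 0.65 | 0.70 |
| 12 v 13 | 0.68 | 0.72 | 0.78 |

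The optimism thus runs from 0.63 − 0.50 = 0.13 to 0.78 − 0.50 = 0.28. With 10 to 40 features, apparent sensitivity and specificity are 0.69–0.73 and 0.65–0.67 at 25 v 25, and 0.77–0.80 and 0.70–0.75 at 12 v 13. An unequal split is slightly worse: 8 v 17 with 40 features gives an AUC of 0.80.

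*Multi-feature signature, and whether resampling cures it.* There are 100 null replicates per setting. The top k of p noise features are chosen by mean difference and summed. The score is tested on the same women and on an equal number of new women. Leave-one-out is also run, with selection repeated in every fold.

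| N (recurrences) | k of p | AUC, same women | AUC, new women | Leave-one-out sensitivity + specificity |
|---|---|---|---|---|
| 50 (25) | 1 of 20 | 0.67 | 0.51 | 0.498 + 0.493 = 0.99 |
| 50 (25) | 5 of 100 | 0.86 | 0.51 | 0.496 + 0.482 = 0.98 |
| 50 (25) | 10 of 1000 | 0.97 | 0.51 | 0.516 + 0.516 = 1.03 |
| 20 (10) | 1 of 20 | 0.76 | 0.51 | 0.480 + 0.478 = 0.96 |
| 20 (10) | 10 of 1000 | 1.00 | 0.46 | 0.482 + 0.482 = 0.96 |

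Over all settings run (N = 20, 30 or 50), the same-sample AUC is 0.67–1.00 and the AUC in new women is 0.46–0.51. Leave-one-out sensitivity plus specificity is 0.92–1.03, where chance is 1. Repeating the selection inside patient-level resampling therefore removes the false signal.

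**The case against.** A reader might infer that the recurrence result is bound to be a figure scored on its own design samples, with complete overlap between the two. The article does not support that, for five reasons.

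- **It never says so.** No sentence states that the test will be scored on the samples that shaped it. The Analysis section names sensitivity, specificity and accuracy only for sarcoma versus fibroid, calls the profiles descriptive, and names no recurrence statistic.
- **Internal validation may be specified elsewhere.** Cross-validation or a locked test could sit in the full protocol or SAP, which are not shown. Silence on the method is not itself the fault.
- **The mechanism may not apply.** The primary objective is to profile the tumours, which need not involve selection on recurrence. Tumour exome sequencing is planned and the technique is open. A test built from each woman's own tumour variants and fixed before her plasma is read would largely avoid the problem.
- **Later evaluation is foreseen.** The Discussion expects a larger population to determine diagnostic ability and to allow the test to be modified.
- **The size is assumed.** The simulations use invented splits and feature counts, and one value per woman although sampling is serial.

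All five stand as limits on the claim. They do not remove it. The article itself places test design, the search for a recurrence signature and the recurrence objective in one cohort, and it rules out other recurrence plasma. Answering the objective requires some measure of performance in that plasma. A later study does not correct the DOORS-M figure that would be used to plan it.

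**Conclusion.** The point holds as a conditional one. Design and recurrence assessment share DOORS-M plasma, no second set exists in either study, and no separation is stated. If a signature or cut-off is chosen on that plasma, its recurrence sensitivity and specificity will be optimistic unless they are validated by patient.

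For the best single feature, the illustrative apparent AUC is about 0.63–0.78 against a true 0.50. It is higher for multi-feature signatures. These values depend on the assumed recurrence split, number with plasma, number of independent features and selection on recurrence status. They show what could happen and do not estimate what DOORS-M will report. The optimism would be small or absent for a tumour-informed test locked before the plasma is read.

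This is a secondary objective in an exploratory study. The change is still worth making before the stored samples are analysed, while the separation is easy to arrange.

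**What to change.** State, for the DOORS-M recurrence objective, which of these applies:

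- **(a) Lock first.** Fix the marker list and positivity rule before the plasma is read, using each woman's own tumour exome sequencing or tissue markers chosen without reference to her recurrence status. Use of tissue alone is not enough: markers picked from the same women's tumours because they track recurrence would still leak the outcome.
- **(b) Validate by patient.** Where plasma or recurrence outcome is used to choose features or the cut-off, repeat the whole selection in leave-one-patient-out validation. Hold out all of a woman's serial samples together, and report the held-out figures.
- **(c) Label.** Otherwise, present the result as apparent (development) performance only, and not as ability to detect recurrence.

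The cost is wording and some analysis time, with no new patients, samples or assays. The downside is that the figures will be less favourable and somewhat less stable, and a tissue-derived marker set may transfer imperfectly to plasma.
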